**Discussion:**

The H2Oil-timing study will provide insight into whether tubal flushing with oil-based contrast during hysterosalpingography should be incorporated in the initial fertility work-up in women with unexplained infertility as a therapeutic procedure. If this multicenter RCT shows that tubal flushing with oil-based contrast incorporated in the initial fertility work-up reduces time to conception and is a cost-effective strategy, the results may lead to adjustments of (inter)national guidelines and change clinical practice.

**Trial registration number:**

The study was prospectively registered in International Clinical Trials Registry Platform (Main ID: EUCTR2018-004153-24-NL).

**Supplementary Information:**

The online version contains supplementary material available at 10.1186/s12905-023-02385-1.

## Background

Infertility is defined as the inability to conceive within one year of unprotected intercourse and affects approximately one out of six couples [1]. In these couples fertility work-up can be performed to identify an underlying cause for infertility, which is found in approximately 70–85% of the cases. The most prevalent causes of infertility are ovulation disorders, tubal disease and male factor infertility. In the remaining part of the infertile couples the reason for infertility is unexplained [2, 3].

An essential component of the fertility work-up includes evaluating the risk for tubal pathology based on women’s medical history and Chlamydia IgG antibody test (CAT), and if indicated examining tubal patency through tubal patency testing [4, 5]. Hysterosalpingography (HSG) is typically the preferred method for tubal patency testing during the fertility work-up. Although HSG was introduced as a diagnostic test, the fertility enhancing effect of tubal flushing with oil-based contrast during HSG has been debated for decades [6–8]. In 2017, a large multicenter randomized controlled trial (RCT, H2Oil study) demonstrated that in women with unexplained infertility undergoing HSG with oil-based contrast this resulted in 11% more ongoing pregnancies compared to HSG with water-based contrast. The subsequent live birth rate was also significantly increased [9]. This fertility enhancing effect of oil-based contrast during HSG is confirmed in two recent meta-analyses [10, 11] and a Cochrane systematic review [12]. The latter included six RCTs comparing pregnancy rates within six months after tubal flushing with oil- versus water-based contrast during HSG (odds ratio (OR) 1.42; 95% confidence interval (CI) 1.10 to 1.85) and four RCTs comparing tubal flushing with oil-based contrast during HSG versus no tubal flushing (OR 3.54; 95% CI 2.08 to 6.02) [12].

The confirmation of the fertility-improving benefits of tubal flushing with oil-based contrast in women with unexplained infertility has expanded the role of HSG beyond its diagnostic function during fertility work-up. The next knowledge gap that needs to be addressed is determining the optimal timing for performing tubal flushing in relation to the fertility work-up considering its therapeutic role as well. In the Netherlands, the timing of start of fertility treatment for couples with unexplained infertility is based on their prognosis for natural conception within twelve months, and is estimated using the prognostic model of Hunault [13, 14]. In couples with a favorable prognosis, i.e. above 30%, expectant management is advised for a period of at least six months followed by intra-uterine insemination (IUI) in absence of the achievement of pregnancy. HSG is usually performed by the end of the period of expectant management. However, considering the therapeutic aspect of tubal flushing, an HSG performed during the fertility work-up instead of six months after the expectant management period might lead to a shortened time to conception.

The aim of this study is to evaluate the optimal timing for therapeutic flushing in couples with unexplained infertility. In this study we compare the effectiveness and cost-effectiveness of immediate tubal flushing with oil-based contrast during HSG incorporated in the fertility work-up compared to delayed tubal flushing that is performed six months after the fertility work-up is completed. We hypothesize that immediate tubal flushing (integrated in the fertility work-up) is a cost-effective strategy leading to a shorter time to pregnancy, more live births and less expensive and invasive fertility treatments compared to delayed tubal flushing.

## Methods

This study is an investigator-initiated, open label, multicenter, randomized controlled trial performed in the Netherlands and the United Kingdom. Participating hospitals include district, teaching and university hospitals, listed in appendix A. The study has granted ethical approval by the National Central Committee on Research involving Human Subjects (CCMO – NL 62838.029.18), by the Ethics committee of the Amsterdam UMC, location Vrije Universiteit Amsterdam (Ref. No. 2018.291, date 25th of July 2019) and by the boards of all participating hospitals. The study is also approved by the Research Ethics Committee London Harrow in the UK (Ref. No. 20/LO/0608, date 1st of July 2020). The first participant is enrolled on the 22nd of August 2019.

### Study population

In this study we will include women with unexplained infertility between 18 and 39 years of age, who have a regular ovulatory cycle (defined as eight or more spontaneous menstrual cycles per year), who are at low risk for tubal pathology and have been advised expectant management for at least six months. Women will not be included if they are at high risk for tubal pathology, defined as history of pelvic inflammatory disease, chlamydia infection, positive CAT, peritonitis, intestinal surgery, surgery of the Fallopian tubes and/or ovaries and endometriosis. Women are excluded if they have endocrine disorders (except for well managed hypothyroidism with thyroid-stimulating hormone (TSH) concentration < 2.5 mU/L) or iodine contrast medium allergy. Infertility is defined as the failure to achieve pregnancy after at least twelve months of unprotected intercourse. The male partner or sperm donor should have normal or mild impaired semen quality, defined as a pre-washed total motile sperm count (TMSC) above 3 × 10^6^ spermatozoa per milliliter. Inventory of the medical history, physical examination and blood tests will be done during the fertility work-up, which determine if expectant management is advised.

### Recruitment, randomization and blinding

Eligible women will be identified by their clinician during the fertility work-up. Counselling for the study will be done by a trained research staff member and all women will receive written information. Couples will be given a minimum of two days to consider participation. Those women who agree to participate will be asked to sign a written consent form. After informed consent, women will be randomly allocated to the intervention group (immediate HSG) or control group (delayed HSG). Randomization will be performed via the web-based application Castor Electronic Date Capture (EDC, Amsterdam, the Netherlands) with the use of permuted block design stratified per center (block size: 4, 6 or 8). Owing to the nature of the intervention and since our primary outcome of time to conception leading to live birth is objective, the trial is not blinded. After randomization the data will be collected in an electronic case report file (eCRF), using Castor EDC. All study procedures will be performed by clinicians and other research employees trained according to the Good Clinical Practice guidelines.

### Outcomes

The primary outcome is time to conception leading to live birth, with the first day of the last menstrual bleeding before a positive pregnancy test within 12 months after randomization. We will assess the presence of this endpoint also at six months after randomization as a co-primary outcome. All outcomes are listed and described in Table 1.

**Table 1 Tab1:** Outcomes and descriptions

**Primary outcome**	**Definition/measurement**
Time to conception leading to live birth measured at 6 months	Calculated from the first day of the last menstrual bleeding before a positive pregnancy test
Time to conception leading to live birth measured at 12 months	Calculated from the first day of the last menstrual bleeding before a positive pregnancy test
**Secondary outcome**	**Definition/measurement**
Biochemical pregnancy	A positive pregnancy test or serum HCG-level greater than 5 IU/L
Clinical pregnancy	Gestational sac visible on ultrasonography
Ongoing pregnancy	Positive heartbeat at 12 weeks of pregnancy on ultrasonography
Miscarriage	Non-vitality on ultrasound or spontaneous loss of pregnancy
Ectopic pregnancy	No intrauterine gestational sac with an ectopic gestational sac and/or persistent serum HCG levels
Multiple pregnancy	Pregnancy of two or more fetuses
Complications after HSG	All adverse events occurring within one month after HSG procedure, for example pelvic infection, intravasation and allergic reaction
Level of pain during HSG	Reported on VAS (scores: 0.0 to 10.0 cm)
Thyroid function after HSG	Serum FT4 and TSH one month after HSG
Used fertility treatments	IUI, IVF, ICSI
Pregnancy complications	E.g. pregnancy induced hypertension, gestational diabetes, still birth
Pregnancy outcomes	E.g. gestational age, pre-term birth, birth weight
Cost-effectiveness	Effectiveness: time to conception leading to live birth Costs: Healthcare perspective: costs for HSG and fertility treatments Societal perspective: healthcare costs, loss of productivity costs and patient costs (care services paid for by the patients themselves) using iMCQ and iPCQ

HCG: human chorionic gonadotropin, HSG: hysterosalpingography. VAS: Visual Analogue Scale, FT4: free thyroxine, TSH: thyroid-stimulating hormone, IUI: intrauterine insemination, IVF: in vitro fertilization, ICSI: intracytoplasmatic sperm injection, iMCQ: Medical Consumption Questionnaire, iPCQ: Productivity Cost Questionnaire

### Description of intervention

Women allocated to immediate HSG will undergo their HSG preferably in the month following randomization and will subsequently have expectant management for at least six months if the HSG findings are normal.

### Description of control

Women allocated to six-months delayed HSG will have expectant management for six months followed by undergoing HSG, if an ongoing pregnancy was not achieved in the meantime.

### HSG procedure

In both arms, tubal flushing during HSG will be performed according to the local protocol of each participating center during the follicular phase of the menstrual cycle after complete cessation of menstrual bleeding. The HSG will be undertaken using oil-based contrast (Lipiodol® Ultra Fluid, Guerbet, Villepinte, France). Prior to the HSG women will be asked to fill out the modified Amsterdam Preoperative Anxiety and Information Scale (APAIS) questionnaire to assess their pre-procedural anxiety level [15]. During the HSG, oil-based contrast medium will be infused into the uterine cavity through a special HSG-balloon catheter, a cervical vacuum cup or a metal/acorn cannula. The maximum recommended volume of the contrast medium is 15ml to limit women’s exposure to iodine. Batch number and expiration date of the used contrast medium will be reported for drug accountability. During infusion of the contrast under fluoroscopic control four to six radiographs or images will be taken to evaluate the filling and shape of the uterus and the patency of the Fallopian tubes. Immediately after the procedure women’s pain experience will be evaluated, using the Visual Analogue Scale (VAS) ranging from 0.0 to 10.0 cm. According to local protocols, in some cases a final radiograph may be taken 20 to 30 min later to evaluate the dissemination of the contrast in the abdominal cavity. Antibiotic therapy (e.g. Doxycylin 200 mg BDS for 7 days) will be prescribed in case of suspected intra-abdominal adhesions or hydrosalpinx, according to the local protocols of the participating centers. The procedure will be immediately discontinued if an allergic reaction occurs or intravasation of the contrast medium is noticed on the radiographs to minimize to risk of oil-embolism. The HSG radiographs and images will be evaluated by a gynecologist and/or radiologist according to the local protocol of the participating centers.

### Follow-up

For the primary study, we will follow-up women for twelve months, with conception rates assessed six and twelve months after randomization. For each conception within twelve months after randomization, we will assess whether this conception leads to live birth beyond the twelve months window. Follow-up outcome data will be extracted from women’s medical records and/or by sending a digital questionnaire send to them through Castor EDC. The follow-up data include information about fertility treatments (used to calculate direct medical costs), (ongoing) pregnancy(ies) and delivery if applicable. At six and twelve months after randomization women will receive a digital questionnaire send through Castor EDC to explore indirect costs from a societal perspective during the preceding six months (iMCQ [16] and iPCQ [17]). Table 2 provides an overview of the study activities. For a secondary analysis, we will follow women until 36 months after randomization.

**Table 2 Tab2:** SPIRIT schedule of enrollment, intervention and assessments

	Study period					
	Enrollment	Allocation	Post-allocation			
TIMEPOINT	-t_1_	t_0_	t_1_	t_2_	t_3_	t_4_
ENROLLMENT:						
Eligibility screening	X					
Informed consent	X					
Allocation		X				
INTERVENTIONS:						
Immediate oil-HSG			X			
Delayed oil-HSG				X		
ASSESSMENTS:						
Baseline characteristics		X				
APAIS questionnaire*			X or X			
Pain score*			X or X			
HSG procedure, results and complications*			X or X			
iMCQ				X	X	
iPCQ				X	X	
Fertility treatment					X	
Pregnancy yes/no				X	X	
Ongoing pregnancy outcome						X

*Depending on the allocated intervention. -t_1_: prior to allocation, t_0_: at allocation, t_1_: first menstrual cycle after allocation, t_2_: 6 months after allocation, t_3_: 12 months after allocation, t_4_: 2 months post-partum

### Sample size

The time-to-event method was used for the sample size calculation, based on the study of Dreyer et al. [9]. The expected cumulative live birth rate in the control group is 53% with a median time to event of 11 months in the control group. A two-sided log rank test with an overall sample size of 554 subjects achieves 90% power at a 0.05 significance level to or refute a statistically significant effect with a hazard radio of 1.39. It is assumed that 0.32% of the couples switch from one group to the other group. Sample size calculation was done using PASS 15.0.6 (NCSS Statistical Software LCC, Utah, USA).

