**Methods:**

This study will be an investigator-initiated, open-label, international, multicenter, randomized controlled trial with a planned economic analysis alongside the study. Infertile women between 18 and 39 years of age, who have an ovulatory cycle, who are at low risk for tubal pathology and have been advised expectant management for at least six months (based on the Hunault prediction score) will be included in this study. Eligible women will be randomly allocated (1:1) to immediate tubal flushing (intervention) versus delayed tubal flushing (control group) by using web-based block randomization stratified per study center. The primary outcome is time to conception leading to live birth with conception within twelve months after randomization. We assess the cumulative conception rate at six and twelve months as two co-primary outcomes. Secondary outcomes include ongoing pregnancy rate, live birth rate, miscarriage rate, ectopic pregnancy rate, number of complications, procedural pain score and cost-effectiveness. To demonstrate or refute a shorter time to pregnancy of three months with a power of 90%, a sample size of 554 women is calculated.

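### With the primary outcome limited to conceptions within 12 months, 554 women give about 84% power for a hazard ratio of 1.39, not the stated 90%

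*Protocol article*

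**What the plan says.** The Sample size section of the protocol article gives these design inputs:

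- Test, size and power: "A two-sided log rank test with an overall sample size of 554 subjects achieves 90% power at a 0.05 significance level".
- Effect: "statistically significant effect with a hazard radio of 1.39" (the word radio is evidently a misprint for ratio).
- Control arm: "The expected cumulative live birth rate in the control group is 53% with a median time to event of 11 months in the control group".
- Switching between groups: 0.32% of couples.

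The abstract (Methods) expresses the same target in time: "To demonstrate or refute a shorter time to pregnancy of three months with a power of 90%, a sample size of 554 women is calculated". It also gives 1:1 allocation.

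The window is set elsewhere. The abstract, the Outcomes section and the Statistical analyses section all define the primary outcome by conception within 12 months of randomization. The Follow-up section says: "For the primary study, we will follow-up women for twelve months". Later follow-up there serves two other purposes. One is to learn whether a conception within the window ended in live birth. The other is a secondary analysis to 36 months.

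**The concern.** The power of a log-rank test depends on the number of events, not directly on the number of women. A hazard ratio of 1.39 at two-sided 0.05 with 90% power needs events in about 70–71% of 554 women. The plan expects 53% in the control arm, and the hazard ratio then implies about 65% in the intervention arm. The average of about 59% falls clearly short.

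The 90% figure describes the main test of the trial and appears in both the abstract and the Methods. A reader of a non-significant result would take the chance of having missed a true hazard ratio of 1.39 to be 10%, when the plan's own inputs put it at about 15–16%. The article says the results may change guidelines, so the figure should be right.

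**Working it through.** **Inputs.** From the Sample size section: N = 554, two-sided alpha 0.05, hazard ratio (HR) 1.39, control rate 53%, control median 11 months. From the abstract: 1:1 allocation, so 277 per arm. From the abstract, Outcomes, Follow-up and Statistical analyses sections: events count up to month 12. Assumptions: proportional hazards and no loss to follow-up. The second favours the plan.

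**1. Do the control inputs agree?** With exponential times and median 11 months, the 12-month rate is 1 − 0.5^(12/11) = 0.5305. This matches the stated 53%, so the control rate belongs to a 12-month horizon.

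**2. Events needed for 90% power.**

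- Schoenfeld: 4 × (1.960 + 1.282)² / (ln 1.39)² = 4 × 10.507 / 0.10844 ≈ 388.
- Freedman: (1.960 + 1.282)² × (2.39 / 0.39)² = 10.507 × 37.555 ≈ 395.

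As a share of 554 this is 70.0% and 71.2%.

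**3. Events expected by month 12.**

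- Control: 0.5305.
- Intervention: 1 − (1 − 0.5305)^1.39 = 0.6504. This step needs only proportional hazards. Starting from 0.53 directly gives 1 − 0.47^1.39 = 0.650, whatever the shape of the curve.
- Total: 277 × (0.5305 + 0.6504) ≈ 327 events, mean proportion 0.5905.

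The shortfall is 61 events by Schoenfeld and 68 by Freedman.

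**4. Power with 327 events.**

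- Schoenfeld: Φ(√327.1 / 2 × ln 1.39 − 1.960) = Φ(2.978 − 1.960) = 84.6%.
- Freedman: Φ(√327.1 × 0.39 / 2.39 − 1.960) = Φ(2.951 − 1.960) = 83.9%.
- Simulated log-rank test, exponential times censored at 12 months, 40,000 runs: 84.1%.

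The stated 90% is not reproduced. The choice of formula moves the result by less than one point, against a gap of more than five.

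**5. Effect of the stated switching.** With 0.32% switching in the simulation, power is still about 84% (84.3%, within simulation error of the figure without switching). It does not explain the gap.

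**6. What 90% would take in a 12-month window.**

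- At HR 1.39: 387.6 / 0.5905 ≈ 656 women (Schoenfeld) or 394.6 / 0.5905 ≈ 668 (Freedman).
- With 554 women: HR of about 1.43, which gives about 330 events and power of 90.1% (Schoenfeld) or 89.5% (Freedman).

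**7. Settings that do reach 90% with 554 women.**

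- A one-sided 0.05 test at 12 months: 90.9% (Schoenfeld), 90.4% (Freedman). The text says two-sided.
- Counting events over about 16–17 months per woman: 90.0% at 16.2 months (Schoenfeld), 90.1% at 17 months (Freedman). The text stops at 12 months.

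**The case against.** The best defence is that this is a condensed article. The sample-size software may have been given accrual and follow-up settings that are not printed, and under those settings 554 may be correct. That is possible: an assumed 9 months of accrual plus 12 months' minimum follow-up returns 554, and so does 24 plus 6. But every such setting counts conceptions after month 12, which the primary outcome excludes. It might explain how the figure arose, but it would not make the figure right for the stated outcome. Because several unrelated settings fit, a reader should not infer which one was used. Nor is the absence of the software inputs from an article a fault.

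Other parts of the defence stand, and they limit the point:

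- **Three months against 1.39.** A reader might see a conflict, since 11/8 = 1.375. But 11/1.39 = 7.9 months, a gain of 3.1 months, so three months is a fair rounding. The design effect is 1.39, and power should be judged at that value.
- **Lower power from losses or heavier switching.** A reader might push the figure below 84% by assuming such rates. The article gives no loss rate and sets switching at 0.32%, so any such figure rests on inputs from outside the document. Losses would lower power, but by an amount the document does not let one state.
- **The word refute.** It might be read as a plan to treat non-significance as proof of no effect. The Statistical analyses section puts the emphasis on estimates with 95% confidence intervals, so this is mainly a matter of wording.
- **Seriousness.** Power of about 84% is still above the common 80% benchmark. Type I error, the outcome definition and the analysis are untouched.

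**Conclusion.** The stated 90% power is wrong for the design as written. On the plan's own inputs and 12-month window, 554 women give about 327 events against the 388–395 needed, and power of about 84% (83.9–84.6% by formula, 84.1% by simulation). The type II error at a hazard ratio of 1.39 is about 15–16%, not 10%.

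This rests on proportional hazards through month 12 and on no loss to follow-up. The second assumption favours the plan. The first probably does too, since control women who have not achieved an ongoing pregnancy are offered the procedure at six months. Exponential times are used only to confirm that the 53% is a 12-month rate, and in the simulation.

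The document does not support a claim that the trial is too small to be informative, nor that the cause of the discrepancy is known. The point is a correction to a stated power figure.

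**What to change.** Keep 554. In the Sample size section and the abstract, replace 90% with about 84% power for a hazard ratio of 1.39 in a two-sided 0.05 log-rank test, with about 327 events expected by 12 months. An equivalent statement is that 554 women give 90% power for a hazard ratio of about 1.43. If the 90% was obtained with follow-up beyond 12 months, recompute it for the 12-month primary window and report that value.

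The cost is a text change in two places and a less favourable stated power. No extra participants are needed, and conduct and analysis stay as planned.

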### Statistical analyses

The primary analysis will be performed according to the intention-to-treat principle. Continuous variables that are normally distributed will be summarized as means with standard deviation and, if not normally distributed, as medians with an inter-quartile range. Dichotomous data will be reported as proportions with percentages. We will summarize recruitment numbers, lost to follow-up, protocol violations and other relevant data.

The effectiveness of a fertility work-up with a strategy of immediate tubal flushing during HSG versus a strategy of six-month delayed tubal flushing during HSG will be expressed as a rate of live birth with corresponding 95% confidence intervals. Time to pregnancy will be compared in both groups using Cox Proportional-hazards analysis.

Dichotomous outcomes will be analyzed using either modified Poisson regression or logistic regression as appropriate. Continuous outcomes which are normally distributed will be analyzed using linear regression and if outcomes are non-normally distributed negative binomial regression will be used. Although p-values will be reported, the focus will be on providing Risk Ratios for effectiveness with 95% confidence intervals around them as these are more useful in interpreting the findings of the trial.

For losses to follow-up, protocol violations and missing data, we will attempt worst-case scenario analysis to explore the effect of these factors on the trial findings. As a sensitivity analysis, we will explore the effects of missing data on the trial findings using imputation techniques.

Apart from the analysis for the primary outcome – time to conception within twelve months leading to live birth - we will also perform an analysis comparing the time to conception and number of conceptions within 6 months after randomization that lead to live birth. This will allow us to assess the effect of immediate flushing with oil-based contrast as compared to no flushing.

Apart from the intention-to treat analysis, we planned a per protocol analysis. We will write a separate statistical analysis plan that will specify the details of this analysis. SPSS software (IBM) and R software (R Project for Statistical Computing) will be used for all statistical analyses.

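### The analysis section stresses live-birth rates and risk ratios and words the Cox event as pregnancy, which does not match the defined and powered outcome, time to conception leading to live birth

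*Protocol article*

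**What the plan says.** - **Outcomes:** "The primary outcome is time to conception leading to live birth", within 12 months of randomization. The six-month time point is added: "We will assess the presence of this endpoint also at six months after randomization as a co-primary outcome". Table 1 lists biochemical, clinical and ongoing pregnancy, miscarriage and ectopic pregnancy separately, as secondary outcomes.
- **Abstract, Methods:** "We assess the cumulative conception rate at six and twelve months as two co-primary outcomes". The same paragraph states the target effect as a gain of three months in time to pregnancy.
- **Sample size:** "A two-sided log rank test with an overall sample size of 554 subjects" is said to give 90% power at the 0.05 level for a hazard ratio of 1.39. The control group is assumed to have a cumulative live birth rate of 53% and a median of 11 months.
- **Statistical analyses:** the effectiveness of the two strategies "will be expressed as a rate of live birth with corresponding 95% confidence intervals". The next sentence reads "Time to pregnancy will be compared in both groups using Cox Proportional-hazards analysis". Further on, "the focus will be on providing Risk Ratios for effectiveness with 95% confidence intervals around them". A later paragraph names the primary outcome correctly, but attaches no test or effect measure to it.
- **Description of control:** women in the delayed arm undergo HSG after six months unless an ongoing pregnancy has been achieved.

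**The concern.** The trial asks whether flushing at the work-up brings conception forward. The outcome definition and the sample size answer that on a time scale. The analysis section departs from this in two ways.

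1. **Event.** The Cox sentence says pregnancy. The defined event is a conception that ends in live birth. Taken literally, the model would count conceptions later lost to miscarriage or ectopic pregnancy, which Table 1 keeps apart from the primary outcome.
2. **Effect measure.** The stated emphasis is on a proportion and a risk ratio. At 12 months these ignore when conception occurred, and by then the control strategy includes the same flushing. A gain that is purely one of timing can shrink or vanish on that scale.

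At stake is which number carries the conclusion. The trial is open-label, and a live-birth risk ratio, a hazard ratio for pregnancy and a hazard ratio for the defined outcome could point to different conclusions. The text should settle this before results are known.

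**Working it through.** **Inputs.** From Sample size: control median 11 months, control rate 53%, hazard ratio 1.39, two-sided alpha 0.05, 554 women. From the Abstract: 1:1 allocation, so 277 per arm. From Description of control: HSG at month 6. Assumptions of this check: exponential times, and the catch-up patterns in steps 4 and 5.

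**1. The plan's own figures.** λ = ln 2 / 11 = 0.0630 per month. Control at 12 months: 1 − exp(−12λ) = 0.531, which agrees with the stated 53%. The median under immediate flushing is 11 / 1.39 = 7.9 months, a gain of 3.1, which agrees with the three months in the Abstract. The powered effect is therefore a hazard ratio for a time.

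The 554 is not reproduced. Schoenfeld's formula gives 4 × (1.960 + 1.282)² / (ln 1.39)² = 388 events. With a mean event probability of (0.53 + 0.65) / 2 = 0.59, that is about 658 women. This is a separate matter and does not decide the present point. The powers below are those that 554 women give.

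**2. Formulas.**
- Log-rank power = Φ(½ · √events · ln 1.39 − 1.96).
- Risk-ratio power, taken as the two-proportion test = Φ[(difference − 1.96 · pooled SE) / unpooled SE].

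**3. Constant hazard ratio for 12 months.**
- Immediate arm: 1 − exp(−1.39 × 12λ) = 0.650. Risk ratio 0.650 / 0.531 = 1.23.
- Events: 277 × (0.5305 + 0.6504) = 327. Log-rank: ½ × 18.09 × 0.3293 − 1.96 = 1.02, power 84.6%.
- Risk ratio: (0.1199 − 1.96 × 0.0418) / 0.0415 = 0.92, power 82.0%.

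**4. Control hazard also rises by 1.39 from month 6 (assumption).**
- Control at 12 months: 1 − exp(−6λ − 1.39 × 6λ) = 0.595. Risk ratio 0.650 / 0.595 = 1.09.
- Risk ratio: (0.0555 − 1.96 × 0.0412) / 0.0411 = −0.61, power 27.0%.
- Log-rank, by simulation: about 42%.

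**5. Effect lasts six months after each arm's own HSG (assumption).** Both arms reach 0.595 at 12 months, so the risk ratio is 1.00 and its test rejects at about its 5% level. The log-rank test rejects in about 10%.

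**6. Six months.** Rates are 1 − exp(−6λ) = 0.315 and 1 − exp(−1.39 × 6λ) = 0.409, risk ratio 1.30. Log-rank with 277 × 0.7236 = 200 events: 64.5%. Risk ratio: 63.4%.

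**7. Simulation** (4,000 trials per scenario, 277 per arm; a separate run agreed within 2 percentage points):

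| Scenario | Log-rank, 12 mo | Risk ratio, 12 mo | Log-rank, 6 mo | Risk ratio, 6 mo |
|---|---|---|---|---|
| Constant 1.39 | 84.4% | 82.6% | 63.9% | 62.5% |
| Control also 1.39 from month 6 | 41.7% | 26.8% | 62.3% | 61.3% |
| Effect six months only, each arm | 10.3% | 5.4% | 65.1% | 63.8% |

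**The case against.** The strongest reply is that this is loose wording in a condensed article.

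- A Cox comparison is planned, the primary analysis is by intention to treat, and the same section later names the primary outcome correctly. The Abstract and the Background also use time to pregnancy as shorthand, and Table 1 has no other clinical time-to-event outcome. **This stands.** A reader might infer that the primary outcome has no planned analysis, or that losses will certainly be counted. The document does not support either; it supports only that the event is worded differently from its definition.
- The risk-ratio sentence sits in the paragraph on regression for dichotomous and continuous outcomes, so it may concern those only. **This stands in part.** The separate sentence giving effectiveness as a live-birth rate is about the main comparison of the two strategies.
- The Abstract makes cumulative conception rates co-primary, so a proportion belongs to the primary objective. **This stands.** It is also a further version of the primary outcome that has to be reconciled.
- The log-rank test is the score test of the Cox model, so these are one analysis and not two rivals. **This stands.**
- A lasting 1.39-fold catch-up is nowhere stated, and it gives a 59.5% control rate against the plan's 53%. **This stands**, and the size of the loss at 12 months is conditional on it.
- A statistical analysis plan is announced. In its place, that sentence reads as referring to the per-protocol analysis. A later plan could add detail, but the printed mismatch would still need correcting.

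**Conclusion.** The point holds as a mismatch within the article. The outcome and the sample size concern time to conception leading to live birth; the analysis section emphasises a live-birth rate and risk ratios and words the Cox event as pregnancy. The main effect measure is not tied to what was defined and powered.

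Under the protocol's own constant hazard ratio, the cost of relying on the 12-month risk ratio is small, about 82% against 84% power. It becomes material only if controls catch up after their flushing: about 27% against 42% if their hazard rises by the same 1.39, and no power if the arms draw level by month 12. These figures assume exponential times and a catch-up that the documents do not quantify.

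A reader might conclude that the risk ratio is in general the measure least able to show a timing effect. That goes too far: it does not apply at the six-month co-primary time point, where the measures are about equal, and it barely applies under a constant hazard ratio.

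**What to change.** In Statistical analyses, replace the live-birth-rate sentence and the Cox sentence with one statement of the primary analysis:

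- Time from randomization to conception leading to live birth, censored at 12 months, compared by intention to treat with the log-rank/Cox analysis that underlies the sample size. The hazard ratio with its 95% confidence interval is the main effect measure, and cumulative incidence curves are shown.
- The six-month analysis stays co-primary, as the comparison with no flushing, and uses the same event definition.
- Risk ratios at 6 and 12 months are supporting measures. Reconcile this with the Abstract, which makes cumulative conception rates co-primary.
- Time to any pregnancy is secondary and is labelled as such.

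A difference in restricted mean time over 12 months is optional and supporting only. In simulation it had more power than the log-rank test under the catch-up of step 4 (56% against 42%), but less under the protocol's constant hazard ratio (77% against 84%).

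The cost is wording in the protocol and the analysis plan, with no new data. The small downside is that risk ratios, which are easy to interpret, lose their emphasis.
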